#### Secondary objectives

Our secondary objectives include the assessment of treatment fidelity in the two programs, as well as participant willingness to enroll in yoga programs of varying duration and intensity. In addition, we will measure RLS symptom severity, sleep quality, mood, and health-related quality of life at baseline and 12 weeks to obtain effect size estimates for these exploratory outcomes. This information will provide critical data on which to base our planned larger RCT to determine the efficacy of yoga as a potential therapy for RLS. Secondary aims are as follows:Aim.2.1. Monitor and assess treatment fidelity in the yoga and educational film programs, using specific metrics to gauge fidelity. Lapses in fidelity will be recorded and the data used to inform strategies to address these lapsesAim.2.2. Assess the effect sizes at week 12 of a beginner yoga and a structured educational film program for RLS symptoms and related key exploratory outcomes (sleep quality, mood, perceived stress, and health-related quality of life) in adults with moderate to severe RLS, using well-validated, self-report instruments commonly employed in evaluating RLS treatments. Effect size estimates for these exploratory outcomes will provide critical data on which to base sample sizes in future larger trials, as well as provide important preliminary information on sensitivity of specific endpoints to change with a 12-week yoga interventionAim.2.3. Determine acceptable doses of yoga for a trial by assessing participant willingness to complete, as well as preference for yoga programs of the following duration and intensity: 8 weeks, 16 classes (2x/week); 12 weeks, 16 classes (2x/week for first 4 weeks, 1x/week thereafter); 16 weeks, 16 classes (1x/week). Acceptability and preferences will be evaluated using a self-report questionnaire administered to all participants at the follow-up assessment visit

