### Consent and screening

We plan to enroll a minimum of 15 participants for each study cohort; within each cohort, participants will complete their baseline and follow-up assessments within the same 30-day window, and those in the yoga and film groups will begin and complete their respective classes at the same time. All class schedules will be fixed prior to randomization; as in our previous trials, every effort will be made to accommodate participant availability and preferences with respect to class timing.

At visit 1, an investigator will review the informed consent form with each participant in a private room; individuals still interested in participating in the study will sign the consent form. Each participant will sign two copies of the consent form, one to be given to the participant, and one to be stored with the study documents in a locked cabinet in a secure room in the WVU School of Public Health. Participant eligibility will be assessed using the IRLS (question 6) [89, 90] and a standardized screening checklist, similar to that used in our previous trials, which covers all of the eligibility criteria. Hemoglobin (Hb) levels will be assessed noninvasively, using the Masimo Pronto, a simple, hand-held pulse oximetry Hb monitor that has demonstrated excellent reliability and precision in both clinical and healthy populations [103–106]. Reasons for ineligibility and for non-participation of eligible candidates will be documented in a screening log.

Screening evaluations will occur within 30 days prior to the start of the intervention. Participant eligibility will be assessed using a standardized screening checklist similar to that used in our previous trials, which covers the inclusion and exclusion criteria (including RLS diagnostic criteria and at least moderate RLS severity); Hb levels will be assessed using the Masimo Pronto, a simple, hand-held pulse oximetry Hb monitor that has demonstrated excellent reliability and precision [103–106].

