### Interventions

#### Yoga program (active intervention)

Participants randomized to the yoga group will complete a gentle *Iyengar* yoga program based on that developed and successfully implemented in our pilot studies [15, 66]. The yoga program was finalized following detailed review and input from an *Iyengar* Master Trainer.

Program logistics: yoga group participants will attend two 75-min classes per week for the first 4 weeks, then one 75-min class for the remaining 8 weeks, and will be asked to complete a 30-min homework routine 5 days/week on non-class days. Yoga classes will be held at two yoga studios in close proximity to the WVU Health Sciences Center campus (WVU site) and OSU Center for Integrative Health and Wellness (OSU site), respectively. As in our previous trials [15, 66], each yoga class will begin with simple yogic centering and breathing exercises, followed by a sequence of active and restorative poses, and ending with a 10-min guided supine relaxation practice. The yoga routines, including a collective total of 25 common *asanas*, have been tailored for sedentary adults naïve to yoga, gradually increasing in difficulty as students progress. Pose modifications and props (e.g., chairs, blankets, and straps) will be used as needed to enable participants to perform the poses safely and easily, regardless of their level of physical ability or fitness. In addition, each class will be restricted to no more than 12 participants to allow for personalized attention. The home practice (see Table 1) will be performed with the aid of a yoga DVD and a comprehensive, indexed training manual illustrating the homework routines; These guides are based on materials developed for our preliminary trials and modified to reflect the extension to a 12-week intervention period for the proposed study. Participants will also be provided yoga mats and straps to facilitate home practice.

**Table 1 Tab1:** Yoga home practice routines

Home Practice 1: Weeks 1–3 (*use wall for side-angle standing poses*)	
1. Upward extended-leg pose	*Urdhva Prasarita Padasana*
2. Straight-leg pose: (a) bent knee 3x, (b) straight leg 2x	*Supta Padangusthasana*
3. Upward extended arms in mountain pose: (a) palms forward, (b) palms facing	*Urdhva Hastasana in Tadasana*
4. Extended side-angle pose	*Utthita Parsvakonasana*
5. Half-intense pose: (a) hands to wall, (b) hands on chair	*Ardha Uttanasana*
6. Extended triangle pose	*Utthita Trikonasana*

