*Treatment effect sizes* (*A.2.2*), based on between-group differences in change over time, will be estimated using one-way ANOVA models. Effect size estimates will be calculated using both ITT (primary) and per-protocol analyses. These unbiased estimates of intervention effect size will inform sample size determination for our planned future efficacy trial [147]. Scores on *the Yoga-dosing Questionnaire* (*A.2.3*) will also be assessed using descriptive statistics to determine optimal scheduling and maximum acceptable dosing of yoga for our future trial.

*Missing data*: every effort will be made to minimize missing data relevant to all aims. If missing data does occur and the missing-data pattern (probability model) is not missing completely at random (MCAR), then we will consider approaches appropriate for missing at random (MAR) and missing not at random (MNAR). If the pattern or structure of the plausible missing data suggests MAR, either the EM algorithm [148], inverse weighting [149], or multiple imputation (MI) [150, 151] will be used and the missing-data mechanism will be constructed from the collected data [150, 152, 153]. The selected method will reflect the appropriateness of the method to best estimate the underlying missing-data mechanism [148–150, 152]. Participant characteristics will be assessed, including demographic and lifestyle characteristics, RLS severity, medical history, health-related factors, and baseline questionnaire scores for the estimation of plausible models (i.e., MCAR, MAR, and MNAR) for the missing-data mechanism. While we will not be able to definitively test if the missing data are MNAR, If there are indicators suggestive of MNAR (e.g., drop-outs differ significantly from non-drop-outs in key characteristics), we will use MI in conjunction with a sensitivity analysis to provide a set of plausible conclusions recognizing that each conclusion will be predicated on the assumptions necessary for constructing a MNAR missing-data mechanism model [150, 153].

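### The effect-size analysis treats participants taught together in classes as independent, so its precision is overstated if outcomes correlate within class

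*Protocol article*

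**What the plan says.** Participants are randomized individually, 1:1, in randomly varying blocks (Randomization), but both programs are taught in groups. Under Consent and screening: "We plan to enroll a minimum of 15 participants for each study cohort"; "those in the yoga and film groups will begin and complete their respective classes at the same time"; and "All class schedules will be fixed prior to randomization". Under Yoga program, "each class will be restricted to no more than 12 participants to allow for personalized attention". The film sessions are also classes and end in a facilitated discussion (Educational film program).

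Under Statistical methods, effect sizes for the exploratory outcomes are based on between-group differences in change and "will be estimated using one-way ANOVA models". The only factor in a one-way model of that contrast is treatment arm. No class, instructor, cohort or site term is mentioned there. The Sample size section also describes its simulation in terms of an ANOVA and does not mention clustering.

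On use, Aim 2.2 states: "Effect size estimates for these exploratory outcomes will provide critical data on which to base sample sizes in future larger trials". Statistical methods repeats this: "These unbiased estimates of intervention effect size will inform sample size determination for our planned future efficacy trial".

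**The concern.** People who share an instructor, a group and its discussions may end up with more similar outcomes than people in different classes of the same arm. A one-way ANOVA on individuals sets that similarity to zero. Where it is positive, the mean difference stays centred on the right value, but the analysis acts as if it held more independent information than it does, and the interval is too short.

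Two things are at stake. First, the article justifies 44 participants by the precision of the effect-size estimates, so overstated precision touches the stated purpose of the sample size. Second, the estimates go forward to size a trial of the same class-based program. If that trial were sized from them with no allowance for class, it could fall short of its planned power.

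**Working it through.** **Starting point.** The article plans 44 participants and assumes 20% attrition: 44 × 0.8 = 35.2, or 17.6 per arm. The figure of 44 cannot be rebuilt, because the article does not list the simulated effect sizes, standard deviation or target width. Only the attrition step can be followed.

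**Interval under independence.** In SD units, the half-width is t(0.975; 33.2) × √(2/17.6) = 2.034 × 0.337 = 0.69.

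**Completers per class (m), derived.** With at least 15 per cohort, 44/15 = 2.9, so about two or three cohorts.
- Two classes per arm: 17.6/2 = 8.8.
- Three classes per arm: 17.6/3 = 5.9, taken as 6.
- Four classes per arm, if two cohorts each split across the two sites: 17.6/4 = 4.4.

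**Inflation.** The design effect is DEFF = 1 + (m − 1) × ICC, and the half-width is multiplied by √DEFF. The ICC is an assumption.

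| m | ICC | DEFF | √DEFF | Half-width (SD) | Effective n per arm |
|---|---|---|---|---|---|
| 4.4 | 0.01 | 1.034 | 1.017 | 0.70 | 17.0 |
| 4.4 | 0.05 | 1.17 | 1.082 | 0.74 | 15.0 |
| 4.4 | 0.10 | 1.34 | 1.158 | 0.79 | 13.1 |
| 6 | 0.01 | 1.05 | 1.025 | 0.70 | 16.8 |
| 6 | 0.05 | 1.25 | 1.118 | 0.77 | 14.1 |
| 6 | 0.10 | 1.50 | 1.225 | 0.84 | 11.7 |
| 8.8 | 0.01 | 1.078 | 1.038 | 0.71 | 16.3 |
| 8.8 | 0.05 | 1.39 | 1.179 | 0.81 | 12.7 |
| 8.8 | 0.10 | 1.78 | 1.334 | 0.92 | 9.9 |

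**Coverage by simulation.** Each setting used 40,000 trials. Class effects had variance equal to the ICC and were independent between arms, individual variation made up the rest, and the interval was the ordinary pooled one.

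| Classes per arm × size | ICC 0 | ICC 0.01 | ICC 0.05 | ICC 0.10 |
|---|---|---|---|---|
| 2 × 9 | 94.8% | 94.1% | 90.3% | 85.1% |
| 3 × 6 | 95.0% | 94.5% | 92.4% | 88.7% |
| 4 × 4 | 95.0% | 94.8% | 93.2% | 91.3% |

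A longer repeat (400,000 trials per setting) agreed to within 0.4 percentage points for ICC 0.01 to 0.10.

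**Effects shared by both arms.** Adding a cohort effect common to both arms (5% of the variance) with ICC 0 left coverage at 95.2-95.4%. Omitting cohort therefore does not itself shorten the interval. Adding fixed cohort terms did not restore coverage either: for three classes of 6 at ICC 0.05 it moved from 91.7% to 91.5% in one run, and from 92.0% to 91.8% in the longer repeat.

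**Illustration for a later trial.** Suppose a trial were designed for 80% power with no inflation. Its actual power would be Φ(2.802/√DEFF − 1.96). At ICC 0.05 this is Φ(2.802/1.118 − 1.96) = Φ(0.55), about 71%, for m = 6, and Φ(2.802/1.179 − 1.96) = Φ(0.42), about 66%, for m = 8.8. At ICC 0.01 and m = 6 it is about 78%.

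**The case against.** The strongest reply has four parts.

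1. **What goes forward is the estimate.** A reader might infer that the intervals are the planning input for the larger trial, or that the effect size itself is distorted. The documents support neither. Aim 2.2 and Statistical methods carry forward effect-size estimates, and 95% intervals appear only as the precision criterion for 44 participants. Clustering does not bias the mean difference. A reader might also infer that the larger trial will be underpowered, but its sample-size method is not described here. This part of the reply stands. What remains is overstated precision and a later sample size that is not yet committed to allow for class.

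2. **Class effects may be small.** Yoga classes total 16 × 75 min = 20 h, against 30 min × 5 days × 12 weeks = 30 h of home practice, so about 60% of the exposure lies outside class. The film content is standardized, and its instructor mainly leads discussion. Stable class membership and a single instructor per class are inferences, not stated. This is a fair reason to expect a low ICC and rules out an unconditional claim that the intervals are too narrow. It does not justify assuming exactly zero.

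3. **Season, site and cohort effects.** A reader might count these among the causes. Allocation is 1:1 within blocks and both arms of a cohort run together, so whatever they share largely cancels. This stands, and it also removes fixed cohort or site terms as a remedy.

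4. **Few classes, and a possible SAP.** Two to four classes per arm cannot estimate an ICC, and sensitivity analyses are often left to a SAP. The first point argues for an assumed range rather than an estimated ICC. On the second, the article itself names the model, and a SAP that follows it inherits the independence assumption.

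**Conclusion.** The point holds in conditional form. The named model assumes independence in a trial whose two arms are both taught in classes, and it overstates precision to the extent that outcomes correlate within class and arm. At ICC 0.01 the effect is negligible. At 0.05 the interval should be about 8-18% wider than reported, and at 0.10 about 16-33% wider. These figures rest on an assumed ICC, on 20% attrition and on class sizes derived from the cohort minimum.

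The weight is minor to moderate. The outcomes are secondary and exploratory in a feasibility trial, the interval is already wide at about ±0.69 SD, and no decision stated in the article turns on the difference.

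**What to change.** Leave the point estimate as planned. In Statistical methods, under treatment effect sizes, add three things:

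- Report each effect-size interval also with its standard error multiplied by √(1 + (m − 1) × ICC), at ICC 0.01, 0.05 and 0.10, using the observed class sizes.
- Label this a sensitivity range, because the number of classes is too small to estimate the ICC.
- State that any sample size for the larger trial derived from these estimates will allow for class clustering.

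The cost is wording plus class membership for each participant, which the instructors' attendance records should already show. The downside is wider reported intervals: about 2-4% at ICC 0.01 and up to about a third at 0.10.

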### Data collection and outcomes

Assessments will be conducted by study team members with training and experience in clinical assessment; all assessment personnel will be blinded to treatment assignment. Baseline data, including that on exploratory outcomes, will be collected prior to randomization (see “Patient timeline” below).

To determine feasibility and acceptability of the 12-week yoga and educational film comparator program, our primary aim, we will collect comprehensive information, both overall and by treatment group, on: rates of recruitment and success of different recruitment strategies, and reasons for refusal to participate; screening, randomization and enrollment rates, including reasons for screening failures and refusals to enroll/be randomized to treatment; rates of retention (completion of assessment visits) and adherence (completion of home logs and class attendance rates (yoga and film groups); completion of home practice (yoga group)); and participant satisfaction, assessed via a structured *program evaluation questionnaire* regarding participant perceptions of, and experiences with, the study and their respective programs. Attendance data will be collected by the instructor for each group, as will homework logs. Participants will complete the program evaluation questionnaire, modeled on that used in our previous trials [15, 87, 108], upon completion of the 12-week intervention period or upon leaving the study.

A structured questionnaire regarding possible yoga-dosing scenarios will be administered at week 12 to determine participant preferences relative to yoga programs of varying duration and intensity (8 weeks, 16 classes (2x/week); 12 weeks, 16 classes (2x/week for the first 4 weeks, 1x/week thereafter); 16 weeks, 16 classes (1x/week), as well as time of year that the classes meet. Information from this questionnaire will address a secondary aim, and aid in optimizing the yoga protocol for our future studies.

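### As described, the yoga-dosing questionnaire can compare three 16-class schedules but cannot find a maximum acceptable class load, and it misses anyone without a week-12 visit

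*Protocol article*

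**What the plan says.** Aim 2.3, under Secondary objectives in the protocol article, is to find acceptable yoga doses by asking how willing participants would be to complete each of three programs and which they prefer. The programs are "8 weeks, 16 classes (2x/week); 12 weeks, 16 classes (2x/week for first 4 weeks, 1x/week thereafter); 16 weeks, 16 classes (1x/week"). Data collection and outcomes repeats the same three and adds a question on time of year.

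On timing, Aim 2.3 describes a "self-report questionnaire administered to all participants at the follow-up assessment visit", and Data collection and outcomes agrees: "A structured questionnaire regarding possible yoga-dosing scenarios will be administered at week 12". The same section treats the program evaluation questionnaire differently. That form is completed "upon completion of the 12-week intervention period or upon leaving the study".

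Statistical methods then states what the dosing scores are for. They will be summarized descriptively "to determine optimal scheduling and maximum acceptable dosing of yoga for our future trial". Scheduling and maximum dose appear there as two separate products.

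**The concern.** A maximum can be found only if the options reach, or at least approach, a level that some people refuse because it is too much. If the number of classes is the same in every option, the answers carry no information about how many classes would be too many. A result labelled as a maximum would then be a choice among schedules.

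The second issue is who answers. People who found the load too heavy may be over-represented among those who leave, and the dosing form has no stated collection at exit. The sponsor already plans to give another form to leavers, so the gap could be closed.

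At stake is the design of the larger trial. Data collection and outcomes says that this information will help to optimize the yoga protocol for later studies. A schedule preference from people who reached week 12 should not be carried forward as a dose ceiling.

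**Working it through.** **Inputs.** Three options, from Secondary objectives (Aim 2.3) and Data collection and outcomes. Class length of 75 min, and home practice of 30 min on 5 days a week, from Yoga program (active intervention). 44 randomized, 22 per arm, from Randomization. Attrition of 20% planned and 30% considered, from Sample size.

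**Step 1: reproduce the stated class counts.** Classes = sum of (weeks × classes per week).
- 8-week option: 8 × 2 = 16
- 12-week option: 4 × 2 + 8 × 1 = 16
- 16-week option: 16 × 1 = 16

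The stated figure of 16 is right for all three. Class hours are 16 × 75/60 = 20 in each. The range in class load is 16 − 16 = 0.

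**Step 2: what does vary.** Average weekly frequency is 16/8 = 2.0, 16/12 = 1.33 and 16/16 = 1.0. As weeks go up, frequency goes down. No option is heavier on both, none exceeds 2 classes a week, and none exceeds 16 weeks.
- If everyone accepts all three, no ceiling has been found.
- If some refuse one option, they have refused its length or its weekly frequency. They have not refused a number of classes.

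**Step 3: does home practice change this?** The options as listed do not mention it. Assume that the trial's routine applied to each, at 5 × 30 min = 2.5 h a week. Home hours would be 8 × 2.5 = 20, 12 × 2.5 = 30 and 16 × 2.5 = 40, and total yoga time would be 40, 50 and 60 h. Under that assumption total load varies, but it rises exactly in step with program length. A refusal of the longest option could not be assigned to hours rather than weeks.

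**Step 4: who is not asked.** Assume that attrition means no week-12 visit. Number missed = attrition × number randomized.

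| Attrition | Yoga arm (22) | Both arms (44) |
|---|---|---|
| 20% | 4.4, about 4 | 8.8, about 9 |
| 30% | 6.6, about 7 | 13.2, about 13 |

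**Step 5: what the missing answers leave open.** This is an illustration with assumed acceptance counts, which the documents do not give. The lower bound counts every missing person as refusing, and the upper bound counts every one as accepting.
- Yoga arm, 20% attrition, 14 of 18 respondents accept (78%): from 14/22 = 64% to (14 + 4)/22 = 82%.
- Yoga arm, 30% attrition, 12 of 15 respondents accept (80%): from 12/22 = 55% to (12 + 7)/22 = 86%.

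The respondent figure lies inside each interval. The bounds show how much is unknown. They do not show a bias in either direction.

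**The case against.** The strongest reply is that dose here does not mean number of classes. Aim 2.3 describes dose by duration and intensity, and both vary. Holding classes constant while changing the schedule is a legitimate design, and the aim asks for willingness to complete each program as well as preference. This stands in part. A reader might infer that the questionnaire says nothing about dose. The documents do not support that, because it can show which of the offered lengths and frequencies people would accept. It still does not bracket a maximum, for the reason in step 2.

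A reader might also infer that everyone who drops out goes unheard. That is too strong. Retention is defined as completing assessment visits, separately from class attendance, so a person who stops classes but comes at week 12 is asked. The section on discontinuing or modifying interventions allows follow-up, with permission, after the intervention is stopped. Barriers to adherence are recorded, instructors ask non-adherent participants for reasons, and the program evaluation form is collected at exit. These sources may capture complaints about burden, but as described they do not put the three options to leavers.

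Pooling both arms enlarges the count of missed people. Film-arm leavers never did the study yoga, so they cannot have left because its load was too great. The yoga-arm figures are the relevant ones for that mechanism.

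Finally, the form is not shown and could contain an open question on maximum dose. The article describes only the three options and time of year, so the point is limited to the form as described.

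**Conclusion.** The point holds in a limited form. As described, the questionnaire supports the scheduling half of the stated purpose. It cannot support a maximum, because class load is fixed at 16 classes (20 h) and the options trade length against frequency. It also misses participants with no week-12 visit: about 4 of 22 in the yoga arm at 20% attrition and about 7 of 22 at 30%, if attrition is counted that way.

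It would go too far to conclude that the trial's acceptability result is overstated. Acceptability is judged mainly on the Aim 1b benchmarks for retention, attendance, home practice and logs, and Statistical methods evaluates retention and adherence in all randomized participants, so drop-outs count there. Nor can the direction or size of any bias in the dosing answers be computed, because the documents give no acceptance rates for respondents or leavers.

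The aim is secondary and descriptive, and no test or primary benchmark depends on it. The severity is minor.

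**What to change.** 1. Give the dosing questionnaire at week 12 or on leaving the study, together with the program evaluation questionnaire that is already collected at both points.
2. Report the dosing results by arm, with the number randomized and the number not answering beside each percentage.
3. Either reword the sentence in Statistical methods so that it claims willingness and preference among 16-class schedules only, or add an item in which total load varies, with levels for the sponsor to choose.

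The cost is a slightly longer exit form, plus one reworded sentence or one added item. No new visit is needed. Some leavers will still not respond, so the second change is needed even if the first is made.

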### Sample size

We performed a simulation study to determine the total sample size required to derive precise estimates of effect sizes for a two-arm randomized trial using a 1:1 randomization scheme for the primary intervention (yoga) and the educational film program; estimates were based on regression models using multiple simulations and scenarios, and specifically accounting for heterogeneity of effects. We considered seven combinations of effect sizes at 23 different sample sizes for total of 161 effect and sample size combinations. For each combination we ran 5000 simulations for a total of 805,500 simulations. The seven effect-size combinations were structured under the conservative assumption that all interventions would lead to a small to moderate improvement in outcomes and that the yoga intervention would lead to an improvement equal to or greater than the comparator condition. We used repeated simulations to determine the required post-attrition total sample size needed to obtain precise estimates of all three treatment effects under an intent-to-treat (ITT) analysis of variance (ANOVA) analysis. Based on findings of the simulation study and assuming 20% attrition, a sample size of 44 participants will permit reasonably precise estimates (within 95% confidence intervals of the true effect size value) for the two interventions, as well as reasonable estimates of recruitment, randomization, and adherence rates; moreover, estimates remain robust even at 30% attrition. Thus, the study will be adequately powered even if effect sizes for the yoga program are substantially smaller, and attrition rates greater than observed in our pilot studies [15, 66].

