Data on exploratory outcomes and certain modifying/confounding factors will be collected at baseline and 12 weeks to determine the effect sizes of the programs, data critical to the design of the planned larger RCT. RLS symptom severity, the primary efficacy outcome for the full-scale trial, will be evaluated using the International RLS Rating Scale (IRLS), a 10-item scale which includes questions related to frequency, intensity, and impact [89]. Considered the gold standard for measuring RLS symptoms [109, 110], this instrument is recommended for use in RLS clinical trials by the European RLS Study Group (EURLSSG) [111], and is widely used both in the US and internationally [3, 112]. Additional exploratory outcomes are sleep quality, mood, and health-related quality of life (HrQOL), endpoints recommended for inclusion in all clinical trials of RLS [26, 111]. These outcomes will be assessed via a short battery of self-report instruments commonly used in pharmaceutical trials of RLS patients [113–116]. Sleep quality will be assessed using the nine-item Pittsburgh Sleep Quality Index (PSQI) [117]; mood will be evaluated using the 65-item Profile of Mood States (POMS) [118] and 10-item Perceived Stress Scale (PSS) [119, 120]; and HrQOL will be measured using the 36-item MOS Short Form-36 (SF-36) [121, 122]. These self-report instruments are well-established scales that have been shown to be sensitive to short-term behavioral interventions, and have been validated in a wide range of populations, including RLS patients [118, 123–137]. As in our previous trials [15, 66] we will also assess potential changes in blood pressure and heart rate to determine effect sizes in these indices of sympathetic activation; heart rate and blood pressure will be measured three times at each assessment using an automated blood pressure monitor (Omron HEM-780) after a 5-min seated rest period.

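### The only named sign of MNAR, drop-outs differing on measured characteristics, is evidence against MCAR and cannot separate MAR from MNAR, yet it switches on the MNAR sensitivity analysis

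*Protocol article*

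**What the plan says.** All of this is in the protocol article, Statistical methods, missing-data paragraph, unless another section is named.

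- Entry condition: "If missing data does occur and the missing-data pattern (probability model) is not missing completely at random (MCAR"; approaches for MAR and MNAR are then considered.
- MAR branch: "If the pattern or structure of the plausible missing data suggests MAR, either the EM algorithm", inverse weighting or multiple imputation (MI). No sensitivity analysis is attached to this branch.
- Evidence used to judge the mechanism: "Participant characteristics will be assessed, including demographic and lifestyle characteristics, RLS severity, medical history, health-related factors, and baseline questionnaire scores". The items listed are observed variables.
- Caveat: "While we will not be able to definitively test if the missing data are MNAR".
- MNAR branch: "If there are indicators suggestive of MNAR (e.g., drop-outs differ significantly from non-drop-outs in key characteristics", then "we will use MI in conjunction with a sensitivity analysis to provide a set of plausible conclusions".

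Under Data collection and outcomes: "Data on exploratory outcomes and certain modifying/confounding factors will be collected at baseline and 12 weeks". A participant who leaves before week 12 therefore has no exploratory outcome score after baseline.

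Earlier in Statistical methods, the ITT population for the secondary aims is limited to randomized participants who have a baseline assessment and at least one assessment after randomization.

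**The concern.** MAR means that missingness may depend on what was observed but, given that, not on the unseen value. MNAR means that it still depends on the unseen week-12 value after conditioning on what was observed. Drop-outs who differ from completers on age, baseline severity or baseline questionnaire scores are the ordinary MAR situation, which EM, weighting and MI are built to handle. The named indicator therefore fits the protocol's MAR branch as well as its MNAR branch and cannot choose between them.

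The indicator also decides whether the MNAR sensitivity analysis is done. Participants know their assignment, since they open their own envelopes (Blinding section), so leaving because the programme did not help is a plausible route. If those leavers looked like everyone else at baseline, the named indicator would stay silent. The protocol describes the resulting effect sizes as unbiased and intends to size the efficacy trial on them, so an unexamined bias would carry forward.

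**Working it through.** The protocol gives no figure for this rule, so there is none to reproduce. The conclusion follows from the definitions. The numbers below show how the indicator would behave at this trial's size.

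**Inputs.** From the Sample size section: "assuming 20% attrition, a sample size of 44 participants will permit reasonably precise estimates"; 30% attrition is also considered there. 44 × 0.20 = 8.8, about 9 drop-outs and 44 − 9 = 35 completers. 44 × 0.30 = 13.2, about 13 against 31. Assumed, because not stated: two-sided alpha 0.05, a two-sample t-test, and the number of characteristics compared.

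**Power to see a real baseline difference of d SD on one characteristic.** Noncentrality = d × √(n1·n2/(n1+n2)), with 42 degrees of freedom and critical t 2.018.

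- 9 against 35: √(9×35/44) = 2.676. For d = 0.5, noncentrality is 1.338 and power 26%. For d = 0.8 it is 2.141 and power 55%. Power of 80% needs d = 1.07.
- 13 against 31: √(13×31/44) = 3.026. Power is 32% at d = 0.5 and 66% at d = 0.8. Power of 80% needs d = 0.95.

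**Firing by chance under MCAR**, independent characteristics: 1 − 0.95^5 = 23%; 1 − 0.95^10 = 40%.

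**Simulation of the indicator.** 4,000 runs per scenario, N = 44; the indicator fires if any t-test has p < 0.05. Further assumptions: baseline to week-12 correlation 0.5; log-odds of dropout 1.0 to 1.5 per SD of the driving variable; 1 or 6 independent characteristics.

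| What dropout depends on | Fires: 20% dropout, 1 char. | 20%, 6 char. | 30%, 1 char. | 30%, 6 char. | Bias of one arm's mean after baseline adjustment, 20% dropout |
|---|---|---|---|---|---|
| Nothing (MCAR) | 5% | 26% | 5% | 26% | about 0 |
| Baseline score (MAR) | 66–89% | 74–91% | 76–95% | 81–97% | about 0 |
| Part of week-12 outcome unrelated to baseline (MNAR) | 5% | 27% | 5% | 27% | −0.15 to −0.20 SD |
| Week-12 outcome itself (MNAR) | 19–33% | 38–48% | 24–38% | 42–52% | −0.13 to −0.18 SD |

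In every setting the indicator fires most under MAR, where baseline adjustment already removes the bias (−0.09 to −0.11 SD unadjusted at 20% dropout). Under the first MNAR mechanism it fires about as often as under MCAR. Under the second, with 20% dropout and one characteristic, it stays silent in 100 − 33 = 67% to 100 − 19 = 81% of trials.

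**From an arm mean to the effect size.** The last column is bias in one arm's mean, whereas Aim 2.2 estimates a between-group difference. With the same MNAR mechanism in both arms (20% dropout, true effect 0 or 0.5 SD), the bias in the difference is about 0 when dropout depends on the residual part, and 0 to 0.08 SD when it depends on the week-12 outcome. If the mechanism acted in one arm only and the other arm were MCAR, the arm-mean bias would pass to the difference in full: 0.15 − 0 = 0.15 to 0.20 − 0 = 0.20 SD for the first mechanism, and 0.13 to 0.18 SD for the second.

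**The case against.** Several points against this are fair.

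- The indicator is introduced as an example, so others are not excluded, and the same sentence concedes that MNAR cannot be definitively tested. Both stand. Still, no valid indicator is named, and the concession argues for a sensitivity analysis that does not wait for a signal.
- A reader might infer that the plan runs an MCAR test, or that it falls back on complete-case analysis when nothing is significant. The text supports neither. It names no MCAR test and no alpha, never mentions complete-case analysis, and does not say that a null comparison establishes MCAR. Significance appears only inside the example.
- Leaving because of lack of benefit need not be invisible. The programme evaluation questionnaire is also completed on leaving the study, instructors ask non-adherent participants for their reasons, and logs are weekly. These data could inform the missing-data model, although the article does not say that they will.
- Firing under MAR or by chance only adds a sensitivity analysis and does little harm. That stands; only skipping matters.
- A reader might infer that the reported effect would be materially biased. That is not shown: with the same mechanism in both arms the bias is small, and larger bias needs a mechanism that differs by arm.
- The primary aims are feasibility and acceptability, and no hypothesis test is stated for the effect sizes. This limits the stakes.

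**Conclusion.** The point holds in limited form. The one named indicator of MNAR is misclassified: it speaks against MCAR, it is what MAR predicts, and it says nothing either way about MNAR. Tying the sensitivity analysis to it means that the analysis tends to run where it is least needed and could be skipped when drop-outs look like completers at baseline. With about 9 against 35, a real 0.5 SD difference would be missed about 74% of the time (100 − 26). That figure rests on a two-sided 0.05 t-test of a single characteristic; the simulated rates rest on the further assumptions listed with them. The misclassification itself rests on none of these.

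The reach is the exploratory effect sizes of Aim 2.2 and the sample size of the next trial that they inform. A reader might extend the criticism to the primary feasibility results, but this rule does not govern them.

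**What to change.** 1. Delete the drop-out comparison as an example of an MNAR indicator. Use it only to choose covariates for the MAR model. EM, weighting and MI can all stay; preferring one is a matter of choice.
2. Run an MNAR sensitivity analysis whenever week-12 outcomes are missing, for example delta-adjusted MI with the shift allowed to differ by arm. Report how the effect-size estimate moves across the shifts. Since no hypothesis test is stated, the estimate itself is what to track.
3. State that this analysis covers all randomized participants. If the post-randomization assessment in the ITT definition means an outcome assessment, drop-outs fall outside the ITT set and there would be nothing to impute for them. This widens the analysed population, and the text should say so.

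The cost is a few sentences and a few extra model runs. Conduct and data collection do not change.
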